# The safety and efficacy of fecal microbiota transplantation in a population with bipolar disorder during depressive episodes: study protocol for a pilot randomized controlled trial

**DOI:** 10.1186/s40814-021-00882-4

**Published:** 2021-07-14

**Keywords:** FMT, Bipolar disorder, Microbiome, Mood

## Abstract

**Background:**

Bipolar disorder (BD) is a chronic, debilitating illness with significant medical morbidity, often secondary to current treatments, and a high recurrence rate. This burden of disease reflects limitations in the tolerability and efficacy of current treatments. There is a compelling body of evidence linking the gut microbiota to mental illness, and while microbial manipulation via probiotic use has been studied as a therapeutic in BD, targeted trials of fecal microbiota transplantation (FMT) have not been conducted in this population.

**Methods and design:**

We describe a pilot randomized controlled trial of FMT in participants with BD depression to assess the feasibility, efficacy, safety, and tolerability of this intervention. Individuals between 18 and 65 years of age will be enrolled in the study if they meet diagnostic criteria for a major depressive episode of at least moderate severity in the context of a BD diagnosis and have not responded to treatment for BD. Participants will be randomized 1:1 to receive either screened and processed donor stool (allogenic FMT) or their own stool (autologous FMT) via colonoscopy and monitored for 24 weeks post intervention. Depressive and manic symptoms, treatment acceptability, and gastrointestinal and other side effects are assessed at baseline (prior to randomization) and weekly. Stool samples to assess microbiome composition are obtained at baseline and 3 and 6 months.

**Discussion:**

Currently, FMT represents a novel therapeutic option for treating BD depression. This protocol allows for the assessment of the feasibility, efficacy, acceptability, and safety of an intervention aimed at changing the microbiome in those with BD. Results from this pilot study will guide the development of larger trials of FMT for BD depression and may give more insight into how the gut microbiome are altered in those with BD depression.

**Trial registration:**

Clinical Trials Gov NCT03279224

## Background

Bipolar disorder (BD) is a chronic and debilitating condition with an estimated lifetime prevalence of over 2.0% [1]. While the illness is characterized in part by recurring episodes of mania or hypomania, depression accounts for up to 72% of time during which a person is ill [2]. The depressive components of the disorder are also especially challenging to treat and account for clinically significant residual morbidity [3]. A recent review of treatments found no high or moderate strength of evidence for any treatment of the depressive phase of this BD depression [4], supporting research into alternative therapeutic options.

Mounting evidence suggests that the MGB-axis, comprised of neural, humoral, and cellular routes connecting the gut microbiota with the central nervous system (CNS), is perturbed in neuropsychiatric disorders [5]. Essentially, the gut microbiota is able to modulate the MGB-axis both directly and indirectly via endocrine, neural, and immune pathways. In disease or stress states, these pathways may become dysregulated, resulting in intestinal dysbiosis, changes in mood, behavior, and cognition, and altered inflammatory levels [6]. Specific alterations in gut microbiome composition have been identified in individuals with BD [7–10] *and correlate with illness severity* [11]*.* These findings provide a compelling rationale to investigate whether microbiota-targeted interventions have potential for the treatment of BD.

Several strategies for restoring the MGB-axis to a healthy state have been explored in the treatment of psychiatric disorders. As opposed to short-term effects on the microbiome via probiotic [12] and antibiotic administration [13], it is the use of fecal microbiota transplantation (FMT) that may offer the best biotherapeutic option. It increases microbial diversity and does not result in microbiota dysbiosis as does antibiotic treatment. Unlike probiotics, whose colonization appears to be transient, FMT also affords long-term engraftment of the donor strains [14].

To date, no clinical trials have investigated the feasibility and efficacy of FMT in individuals with BD, but a recent systematic review of preclinical and clinical work reported a decrease in depressive and anxiety-like symptoms and behaviours resulting from the transplantation of healthy microbiota, providing support for this area of research [15]. Herein, we present the methodology of a pilot randomized controlled study that evaluates the feasibility of a trial protocol for FMT in participants with BD depression.

The primary objective of this protocol is to evaluate the feasibility of FMT in a BD population and to also examine FMT efficacy in reducing depression severity in BD patients on stable, first-line treatment for BD depression with a prospective, double-blind randomized controlled trial (RCT). This will guide the development of a larger multisite RCT and further our understanding of the potential biotherapeutic potential of FMT. Other secondary objective of the pilot study are to determine the acceptability, safety, and tolerability of FMT in this population.

## Methods

### Trial design

This study is a phase 2/3, double-blind, placebo-controlled RCT (See Fig. 1). Patients with BD on stable, first-line treatment will be randomized to receive either (1) allogenic FMT from a healthy donor or (2) autologous FMT with their own feces. After screening, FMT will be manufactured into an enema and administered via colonoscopy by a trained gastroenterologist. Participants will then be followed for 24 weeks for assessment of primary and secondary study outcomes. We plan to recruit 60 patients: 30 each for the intervention and control groups. This protocol is reported as per the SPIRIT guidelines [16].

**Fig. 1 Fig1:**
[figure not shown]
Trial design. Randomization schema of a pilot randomized controlled trial on the feasibility, safety and efficacy of FMT for Bipolar Disorder. *FMT*, fecal microbiota transplant; *MADRS*, Montgomery–Asberg Depression Rating Scale; *YMRS*, Young Mania Rating Scale; *STAI*, State Trait Anxiety Index; *CGI*, Clinical Global Impressions; *SDS*, Sheehan Disability Scale; *WHOQOL*, World Health Organization Quality of Life; *TSES*, Toronto Side Effect Scale

The study will be conducted at the Psychiatry Department at Women’s College Hospital (Research Ethics Board [REB] # 2017-0099-B), with FMT preparation occurring in the University Health Network/Sinai Health System Department of Microbiology (REB# 17-0289-E) and FMT administration occurring at the endoscopy unit at University Health Network, Toronto Western Hospital (REB#17-5147). All hospital sites are affiliated with the University of Toronto. The study received a No Objection Letter from Health Canada (HC6-0240C201262). To help achieve adequate participant enrolment, flyers have been placed at the recruitment sites, and physicians providing clinical care at these sites have been informed of the study to assist with identification of potentially eligible participants. Physician education about the study has included small and large group presentations, as well as an information sheet.

The active phase of the study involves administration of 1 allogenic or autologous FMT course. Participants are then followed for 24 weeks, with stool samples taken and stored at baseline and 3 and 6 months. All study questionnaires will also be administered at each visit as well as review of side effects experienced. Outcome data collectors, participants, and physicians providing clinical care are blind to study group allocation.

The study is registered with ClinicalTrials.Gov under the identifier NCT02116127.

### Eligibility criteria

Eligible participants must be outpatients between 18 and 65 years of age, have a diagnosis of BD (type I or II) according to the Mini International Neuropsychiatric Interview (MINI) [17], have been on a stable first-line treatment for BD depression as defined in the Canadian Network for Mood an Anxiety Treatment (CANMAT) 2018 guidelines [18] at an adequate dose for ≥ 8 weeks prior to study entry, and currently be suffering from a depressive episode, characterized by a Montgomery–Asberg Depression Rating Scale (MADRS) [19] score at screening and baseline of ≥ 20. Patients will be excluded if they have a Young Mania Rating Scale (YMRS) [20] score of ≥ 12 at screening; meet DSM-IV criteria [21] for substance abuse within the last 6 months or lifetime dependency; have an active eating disorder; have schizophrenia or schizoaffective disorder; have chronic gastrointestinal diseases; conditions causing immunosuppression; a significant bleeding disorder; a history of incomplete colonoscopy; are pregnant or breastfeeding; have regularly used non-steroidal anti-inflammatory drugs, antibiotics, or iron supplements within 3 months prior to study entry; have used prebiotics or probiotics for medical purposes, or have taken antibiotics or any experimental drug within 3 months prior to study entry.

The healthy donors who provided the allogenic FMT will be recruited as part of the Microbial Therapeutics Outcome Program (MTOP) at University Health Network, Sinai Health System and University of Toronto. Potential donors will be excluded if they have a psychiatric disorder according to the MINI [17], a family history in first-degree (blood) relatives of psychiatric illness, a personal or family history of autoimmune disease in first-degree (blood) relatives; anaphylactic food or environmental allergies; diabetes or “pre-diabetes”, defined as HbA1c > 6%; are a smoker (cigarette, marijuana, other); use recreational drugs; regularly consume 2 or more alcoholic beverages daily; and regularly use iron supplements in the 3 months prior to study entry; have a history or symptoms suggestive of underlying gastrointestinal disease; infection or colonization with transmissible agents for repeated donation; active malignancy, or any cancer within the last 5 years, excluding basal cell carcinoma of the skin; risk factors for prion-related disease, including family history of Creutzfeld-Jacob Disease, corneal or dural transplant, or receipt of human-derived pituitary growth factor; history or high-risk status for recent acquisition of HIV, Hepatitis B, or Hepatitis C or sexually transmitted illnesses; immunosuppression; history or physical findings of chronic liver disease or cholestasis; evidence of active encephalitis or meningitis; evidence of active systemic viral, bacterial or fungal infection; receipt of live vaccine in preceding 30 days; receipt of blood transfusion from a country other than Canada in preceding 6 months; history of dementia or degenerative neurological disorders of unknown etiology; recent bite from an animal that may have rabies within the past 6 months; antibiotic use in the 6 months preceding donation; probiotic use for medicinal purposes in the 3 months prior to donation; use of cholestyramine within 3 months of donation; known and current history of blood in stools; and travel outside Canada or the USA in the past 6 months.

To ensure that recipients with severe or anaphylactic reactions to specific foods do not receive FMT from a donor who has recently consumed those foods, dietary screening utilizing a questionnaire developed by the MTOP program will be performed along with the regular prospective screening for medical health, travel and other relevant exposures using a brief checklist for consumption of common allergens. Detailed medical assessment will also be conducted to ensure potential donors are at low risk of infectious disease. This will be further confirmed by stool analysis, free from infectious agents.

### Recruitment

Potentially eligible participants who are willing to hear more about the study receive a detailed study explanation from the study research coordinator. Subjects are provided with a clear explanation of the objectives, procedures, risks, and benefits of the study, and all questions are answered. Questions are asked of subjects to ensure that they understand the nature of the research, risks, and potential benefits of study participation, and their rights as research subjects prior to their signing the informed consent document. The study coordinator will obtain informed, written consent during *Visit 1,* at which time further screening will be performed. The same qualified team members will enroll participants and stool donors. These individuals will not be involved in the clinical care of the patients. To maximize retention, patients will receive reminders of appointments via phone. If a patient misses an appointment, the reason will be investigated, and two attempts will be made to reach them by phone. Participants are given meaningful opportunities during the study to provide ongoing consent for continuation within the study protocol.

### Allocation of interventions

After informed consent is obtained, participants will be randomized to intervention and placebo control groups 1:1, according to a blocked randomization list (4 patients per block), generated in SAS proc PLAN by an individual at the University Health Network not involved in conducting or analyzing the study. Both the participant and study team, except for the lab technologist, will be blinded to group interventions. The allocation list will be kept in sequentially numbered envelopes with the group assignments. The lab technologist will maintain allocation concealment and prepare fecal filtrates for each patient but not be involved in any other part of the study. The researcher performing FMT will receive the designated fecal filtrate labeled only with the participants’ numbers. If an adverse event occurs that is thought to be potentially linked to FMT and requires immediate investigation, the code will be broken only for the affected patient. Only the study physician with the applicable expertise will be unblinded; the rest of the study team will not be informed.

### Intervention

Each participant receives one dose of either autologous or allogenic FMT product. FMT manufacturing will be performed as in a previous RCT (NCT01226992). Briefly, 50 g of screened donor or participant feces will be homogenized for 30 min using a Stomacher® Paddle Blender with 30 mL sterile 0.9 % NaCl + 10% glycerol in a sterile, 330-μn microfilter-separated, double-compartment polyethylene bag. The autologous FMT control arm is essential because bowel preparation and colonoscopy can induce changes to the intestinal microbiome [22, 23]. The volume of fecal filtrate corresponding to 50 g of original feces will be aliquoted, labeled with a recipient ID number to maintain blinding, and stored at – 80 °C. Freezing stool with glycerol as a cryoprotectant has been shown to yield active FMT preparations [24, 25]. For instance, frozen fecal filtrate for treatment of *Clostridium difficile* infection can be stored for at least 6 months in 10% glycerol without loss of clinical efficacy or viability of the six bacterial groups measured [26]. Similarly, clinical efficacy in treating *C. difficile* infection was shown not to differ between frozen and lyophilized FMT product after 9, 11, or 15 months [27]. An aliquot of the final fecal filtrate will be stored at – 80 °C for analysis in case retroactive testing of the fecal filtrate is required.

#### FMT delivery and mucosal biopsies

Prior to colonoscopy, three falcon tubes of frozen fecal filtrate, corresponding to a total of 150 g original donor feces, will be thawed at room temperature over 2.5 h. Thawed feces will be diluted to a total volume of 300 mL with 0.9 N NaCl and packaged into 6 × 50 mL syringes for colonoscopy. The evening prior to colonoscopy, study subjects will take 4L of polyethylene glycol laxative solution. Colonoscopy will be performed by an experienced gastroenterologist at the University Health Network. First, six mucosal pinch biopsies (3 mm size) will be taken: two each from the end of the rectum (20 cm from the anal verge), the ascending colon, and the terminal ileum. These samples will be used for compositional and metabolomic profiling of the mucosa-adherent microbiome. Biopsies will also be sent to pathology if clinically needed. Second, the gastroenterologist will collect 5 mL of colon secretion into sterile microtubes (secretions will be collected via trap). This will be frozen immediately and stored at – 80 °C and used to test for pathogens at the time of FMT in case a recipient develops an infectious disease. Finally, participants will be placed in the right lateral recumbency position, and FMT will be performed with fecal filtrate in one syringe deposited in the terminal ileum and five in the cecum.

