### Data collection, timeline, and outcomes

#### Outcomes

The study visit schedule is detailed in Table 1. A description of the tools used to measure specific outcomes is provided below. The primary outcome measures for the pilot study are (1) feasibility, (2) acceptability, and (3) adherence with the trial protocol.

**Table 1 Tab1:** Study schedule for the participants in the pilot randomized controlled trial of fecal microbiota transplantation (FMT) treatment of bipolar depression

Measure	Study period					Purpose
	Prior to intervention		Intervention	Follow-up (12 visits every 2 weeks)		
	Screening	Baseline	Colonoscopy visit	Every 2 weeks	Week 12 and week 24 visits	
Eligibility screening	**X**					**Feasibility**
Informed consent	**X**					**Feasibility**
Confirmation of eligibility		**X**				**Feasibility**
Randomization		**X**				**Feasibility**
Colonoscopy			**X**			**Intervention**
Anthropometric measurements		**X**		**X**		**Covariates**
Food diary		**X**			**X**	**Covariates**
Mucosa biopsies/colon secretion			**X**			**Microbial analysis**
Stool sample		**X**			**X**	**Microbial analysis**
Blood sample			**X**			**Safety**
Concomitant medications	**X**	**X**	**X**	**X**		**Safety**
Symptoms diary				**X**		**Safety/tolerance**
Toronto Side Effect Scale (TSES)		**X**		**X**		**Safety/efficacy**
Mini-International Neuropsychiatric Interview (MINI)	**X**					**Feasibility**
Young Mania Rating Scale (YMRS)	**X**	**X**		**X**		**Efficacy**
Montgomery–Asberg Depression Rating Scale (MADRS)	**X**	**X**		**X**		**Efficacy**
State and Trait Anxiety Inventory (STAI)		**X**		**X**		**Efficacy**
Sheehan Disability Scale (SDS)		**X**		**X**		**Efficacy**
World Health Organization Quality of Life (WHOQOL-BREF)		**X**		**X**		**Efficacy**

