### Statistical methods

We will use descriptive methods to estimate feasibility and compliance with the FMT intervention, the number of FMT and placebo treatments, the number of fecal samples provided, the duration of follow-up, recruitment rate, rates of nonparticipation, and so on. We will calculate acceptability using reported side effects and patient outcomes.

Variable distribution will be assessed using graphical methods and descriptive statistics, including means, standard deviations, medians and 1st and 3rd quartiles, frequencies and proportions, will be calculated where appropriate. Randomized groups will be compared to assess whether imbalance in covariates such as age and gender are present. For continuous measures (e.g., MADRS scores), change scores will be calculated as the difference between baseline and 6-month visit assessments. Groups will be compared using independent samples *t* test or Wilcoxon signed rank test as appropriate. For binary measures (e.g., proportion of side effects), the difference between groups will be tested using Chi-square or Fisher exact test as appropriate. Bivariate relationships between outcome measures and changes in microbiome composition (e.g., relative abundances of taxa of interest) will be explored using Spearman and Pearson correlation coefficients. For microbiome and metabolome data, multivariate dimensionality reduction approaches, such as Principal Components analysis and cluster analysis, will be employed.

Trajectory plots will be created to examine changes in outcome measures over time. Generalized linear regression models will then be used to assess differences [43] between groups at different time points, as was well as to explore the relationship between these changes and microbiome characteristics. In order to account for correlation between time points, random effects models and generalized estimating equations approach will be used. All models will include group, time, and group by time interaction terms; additionally, factors with known influence on outcome measures will be considered for inclusion as covariates, particularly if found imbalanced between the randomized groups. For patient dropout, the missingness patterns will be assessed, and appropriate methods of handling missing data will be used [44]. Goodness-of-fit will be applied for model diagnostics.

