### Study status

Participant enrollment began February 1st, 2017. We have currently enrolled 25 participants.

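### The post-thaw FMT diluent is printed as 0.9 N NaCl, about 5.8 times the strength of 0.9% saline and most likely a unit error

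*Protocol article*

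**What the plan says.** The protocol article describes two saline steps.

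- **Manufacture (Intervention section).** Each 50 g of feces is homogenized "with 30 mL sterile 0.9 % NaCl + 10% glycerol".
- **Delivery (FMT delivery and mucosal biopsies section).** The starting material is "three falcon tubes of frozen fecal filtrate, corresponding to a total of 150 g original donor feces". The instruction that follows is "Thawed feces will be diluted to a total volume of 300 mL with 0.9 N NaCl". The product goes into six 50 mL syringes, with "one syringe deposited in the terminal ileum and five in the cecum".

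On outcomes, the Outcomes section states: "The primary outcome measures for the pilot study are (1) feasibility, (2) acceptability, and (3) adherence with the trial protocol". The Statistical methods section adds: "We will calculate acceptability using reported side effects and patient outcomes". Under Study status the article reports: "We have currently enrolled 25 participants".

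**The concern.** The numeral 0.9 appears in both saline steps but the unit changes from per cent to normality. Two steps may use two solutions, so the difference alone is not a contradiction. However, the article gives no reason to dilute with concentrated saline, and 0.9% is the strength it uses elsewhere for the same material. The printed instruction therefore most likely names the wrong solution for what is placed in the terminal ileum and cecum.

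If someone followed it as printed, both arms would receive a hypertonic instillate. That bears on gastrointestinal tolerability, and so on acceptability, a primary outcome that draws on reported side effects. It might also affect the viability of the transplanted bacteria, although the article gives no data on viability by salt concentration. The pilot is meant to guide larger trials, so anyone reproducing the procedure needs the right diluent.

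**Working it through.** **Inputs from the article**

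- Manufacturing saline: 0.9%, 30 mL per 50 g of feces, with 10% glycerol.
- Thawed product: three tubes, equivalent to 150 g of feces, hence 3 × 30 = 90 mL of manufacturing saline.
- Final volume: 300 mL.
- Post-thaw diluent: 0.9 N NaCl.

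Physical constants: molar mass 58.44 g/mol for NaCl and 92.09 g/mol for glycerol. NaCl is monovalent, so normality equals molarity.

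**Step 1: the two solutions**

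- 0.9 N: 0.9 mol/L × 58.44 g/mol = 52.6 g/L = 5.26% w/v. Ideal osmolarity is 2 × 900 = 1800 mOsm/L.
- 0.9%: 9 g/L ÷ 58.44 g/mol = 0.154 mol/L. Ideal osmolarity is 2 × 154 = 308 mOsm/L.
- Ratio: 0.900 ÷ 0.154 = 5.84.

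**Step 2: the instillate under a literal reading**

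The filtrate volume V is not given, so a range is assumed. The low end, 90 mL, equals the volume of manufacturing saline. The high end, 240 mL, adds all 150 g of feces at about 1 mL per gram. The only NaCl counted in the filtrate is that from the saline: 90 mL × 0.154 mol/L = 13.86 mmol.

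Final NaCl (mol/L) = [13.86 + 0.9 × (300 − V)] ÷ 300, with V in mL.

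| Filtrate V | Diluent | Final NaCl | Multiple of 0.154 mol/L |
|---|---|---|---|
| 90 mL | 210 mL | (13.86 + 189) ÷ 300 = 0.676 mol/L | 4.39 |
| 150 mL | 150 mL | (13.86 + 135) ÷ 300 = 0.496 mol/L | 3.22 |
| 240 mL | 60 mL | (13.86 + 54) ÷ 300 = 0.226 mol/L | 1.47 |

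If the filtrate is instead taken as 0.154 mol/L throughout, the 240 mL case becomes (36.96 + 54) ÷ 300 = 0.303 mol/L, a multiple of 1.97.

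**Step 3: salt carried by the diluent**

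- 210 mL: 0.210 × 52.6 = 11.0 g at 0.9 N, against 0.210 × 9 = 1.9 g at 0.9%.
- 60 mL: 0.060 × 52.6 = 3.2 g, against 0.060 × 9 = 0.5 g.

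**Step 4: allowing for glycerol**

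If all 90 mL of manufacturing diluent is retained and 10% means w/v, the product holds 9 g of glycerol: 9 ÷ 92.09 ÷ 0.3 L = about 326 mOsm/L. Taking the filtrate as about 300 mOsm/L before glycerol:

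| Filtrate V | 0.9% diluent | 0.9 N diluent |
|---|---|---|
| 90 mL, no glycerol | 306 mOsm/L | 1350 mOsm/L |
| 90 mL, full glycerol | 631 mOsm/L | 1676 mOsm/L |
| 240 mL, no glycerol | 302 mOsm/L | 600 mOsm/L |
| 240 mL, full glycerol | 627 mOsm/L | 926 mOsm/L |

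With glycerol at its upper bound, the literal reading still gives 926 ÷ 627 = 1.5 to 1676 ÷ 631 = 2.7 times the osmolarity of the corrected product.

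**The case against.** The strongest reply is that this is a typographical slip and nobody chose a hypertonic diluent. The N may be loose shorthand for normal saline. The Intervention section contains another unit slip, a filter pore size printed in μn where μm is evidently meant. The article condenses the procedure and refers manufacture to an earlier trial, so staff probably work from a fuller preparation record. The instillate figures rest on a filtrate volume that the article does not give, and the 240 mL end would need about 80 mL in each of three tubes. Retained glycerol could make the product hypertonic even with 0.9% saline. Enrolled participants are also not necessarily treated participants.

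Most of this stands, and it limits the weight of the point:

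- The intent cannot be proved from the text, and misadministration is unlikely.
- The instillate range is conditional on an assumed volume. The 5.84-fold difference between the stock solutions is not.
- Glycerol means that the correction removes the excess due to salt, not necessarily all hypertonicity.

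None of it makes the sentence right. Condensing explains missing detail, not a wrong unit. The reference to the earlier trial covers manufacture and does not clearly reach the post-thaw dilution, which is described separately. A fault in reading the text from PDF is possible in principle, but the per cent signs for saline and glycerol in the Intervention section came through intact.

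**Conclusion.** The concern holds, as a minor point. The printed diluent is 5.84 times as concentrated as 0.9% saline, and nothing in the article corrects or justifies it. A unit error is the most probable explanation but not a certain one. Read literally, the product is hypertonic at every filtrate volume tried: 4.4 to 1.5 times 0.154 mol/L for assumed volumes of 90 to 240 mL, counting only the NaCl from the saline.

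This is an error in a preparation instruction, with a possible bearing on safety and acceptability. The dilution step is described without distinction between the arms, so it does not in itself create a between-arm difference. No figure for sample size, precision or analysis depends on it.

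**What to change.** In the FMT delivery and mucosal biopsies section, change 0.9 N NaCl to 0.9% NaCl. Confirm once, against the preparation record, that 0.9% saline was used for the participants treated so far; the article reports 25 enrolled and does not say how many have been treated. Inform the Data Monitoring Committee only if a different diluent was used. If a concentrated diluent was in fact intended, state its strength and the reason instead.

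The cost is one corrected unit and one record check, with no effect on sample size, analysis or timeline.
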